**Figure 2. F2:**
[figure not shown]
Adjustment of test power as function of total sample size.

### 2.7. Randomization

The type of treatment will be determined randomly for each patient prior to the intervention. Randomization will be generated electronically using the randomizer.org site for the balanced distribution of the children among the groups.

Fifty-two mouth-breathing children with a diagnosis of halitosis will be selected and divided into 4 groups.

Group 1: Treatment with brushing, dental floss and tongue scraper;

Group 2: Brushing, dental floss and aPDT applied to the dorsum and middle third of the tongue;

Group 3: Brushing, dental floss and probiotics;

Group 4: Brushing, dental floss, aPDT and probiotics.

Breath meter results will be determined before, immediately after treatment and 7 days after treatment. Microbiological analysis of the tongue coating will performed at the same times. The quantitative analysis will be performed using direct plating and real-time polymerase chain reaction (PCR).

### 2.8. Interventions

#### 2.8.1. Coated tongue analysis.

The quantity of tongue coating will be defined using the Coated Tongue Index proposed by Shimizu et al.^[29]^ The tongue is divided into 9 parts, each of which receives a score: 0—absence of coated tongue, 1—thin tongue coating with visible papillae, 2—thick tongue coating, papillae not visible.

#### 2.8.2. Breath analysis.

Air from the oral cavity will be collected following the manufacturer’s orientations. The BA will be disinfected after each use. The device will be shaken 4 or 5 times prior to use to eliminate any residual odors. A “beep” is emitted upon opening the upper compartment of the device and a second “beep” is emitted when the volunteer blows into the front air input (passage of airflow). After a third “beep,” the odor of the breath is measured and scored on a scale of 0 to 5 points. An “E” appears when an error has occurred and the procedure is repeated (Fig. 3). A score of ≥2 points is considered indicative of halitosis.

**Figure 3. F3:**
[figure not shown]
Breath odor analysis with breath meter.

To avoid the influence on the breath analysis results, the participants will be instructed to obey the following: in the 48 hours prior to the evaluation, avoid foods with garlic, onion, strong spices, the consumption of alcohol and the use of an oral antiseptic; on the day of the evaluation, abstain from all food in the 2 hours prior to the exam, abstain from coffee, mints, chewing gum, oral and personal hygiene products with perfume (aftershave, deodorant, perfume, creams and tonic) and brush only with water.

#### 2.8.3. Microbiological analysis.

Microbiological collections will be performed before and immediately after treatment. Samples of the tongue coating will be collected with a swab, soaked in reduced Amies medium. The samples will be taken to the laboratory for analysis in less than 2 hours after collection. The samples will be vortexed for approximately 1 minute. After homogenization, 10 serial dilutions will be prepared in 180 μL of sterile phosphate buffered saline. Aliquots of 10–1, 10–2, 10–3, 10–4, and 10–5 will be transferred to Petri dishes with sheep blood agar. As the main bacteria responsible for the production of VSCs are anaerobic, the Petri dishes will be incubated in anaerobiosis for 72 hours at 37°C. Bacterial counts will be based on colony-forming units.^[4,21]^

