## Abstract

**Methods::**

Fifty-two children between 7 and 12 years of age with a diagnosis of mouth breathing and halitosis determined through an interview and clinical examination will be selected. The participants will be divided into 4 groups: Group 1—treatment with brushing, dental floss and tongue scraper; Group 2—brushing, dental floss and aPDT applied to the dorsum and middle third of the tongue; Group 3—brushing, dental floss and probiotics; Group 4—brushing, dental floss, aPDT and probiotics. The use of a breath meter and microbiological analysis of the tongue coating will be performed before, immediately after treatment and 7 days after treatment. The quantitative analysis will involve counts of colony-forming bacteria per milliliter and real-time polymerase chain reaction. The normality of the data will be determined using the Shapiro–Wilk test. Parametric data will be submitted to analysis of variance and nonparametric data will be compared using the Kruskal–Wallis test. The results of each treatment in the different periods of the study will be compared using the Wilcoxon test.

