Alternatives such as aPDT with annatto and the administration of probiotics for the reduction in or elimination of halitosis in pediatric dentistry are less invasive methods that involve natural components, which reduces harm to oral tissues and avoids the occurrence of bacterial resistance. The major challenge is the development of an effective, lasting treatment protocol for halitosis in children that eliminates the anaerobic bacteria related to this condition and reestablishes the microbiota of the dorsum of the tongue, thereby improving quality of life. The use of probiotics in dentistry constitutes innovative treatment capable of modifying the oral microbiota as an alternative to the use of antibiotics and other antimicrobial agents.

The treatment of halitosis is a topic that requires greater attention, and the results of this study can assist in clinical decision making with regards to the use of probiotics and aPDT with blue light-emitting diodes (LEDs) for the treatment of this condition, as most dentists have this light source in their offices and the portable sulfide meter is inexpensive to acquire. Moreover, the use of annatto as a photosensitizer is an innovative approach. As the light source and photosensitizer are accessible, this treatment is expected to be easily and effectively reproducible clinical practice. Probiotics and aPDT are expected to be effective at diminishing halitosis in mouth-breathing children.

The main of the study is to determine whether treatment with aPDT using annatto as the photosensitizer and blue led as the light source is effective at diminishing halitosis in mouth-breathing children.

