#### 2.8.4. Microbiological analysis—real-time PCR.

The samples of coated tongues will be collected with a sterile swab that will be placed in contact with the surface of the dorsum of the tongue with back-and-forth movements. The samples will be placed in tubes containing Tris–EDTA buffer (10 mM Tris—HCL, 0.1 mM EDTA, pH 7.5). The tubes will be duly labeled and stored at −80 °C until analysis. Maximum storage time will be 1 week. The samples will be frozen due to the impossibility of performing all analyses on a single day. After thawing, the samples will be vortexed for 1 minute. The Master Pure DNA Extraction kit (Epicentre Technologies, Chicago, IL) will be used for the extraction of bacterial DNA. First, 100 μL of sample will be eluted in Tris-EDTA buffer. The samples will be centrifuged at 10,000 rpm and 4 °C for 10 minutes. Next, the MIX will be prepared by diluting 300 µL of TCL + 2 µL of Prot K for each sample. The supernatant will be removed with a pipette, with a volume of 25 µL + the formed pellet remaining. Vortexing will be performed for 10 seconds to resuspend the pellet. A total of 302 µL of MIX will be added to each sample, followed by vortexing for 10 seconds and incubation at 65 °C for 15 minutes with vortexing every 5 minutes. The samples will be placed in ice for 5 minutes. A total of 150 µL of MPC (protein precipitation reagent) will be added to the samples, followed by vortexing for 10 seconds. The samples will be centrifuged at 10,000 rpm and 4 °C for 10 minutes. The supernatant will be removed and placed in a new tube, to which 25 µL of MPC (protein precipitation) will be added. The tube will be centrifuged at 10,000 rpm and 4 °C for 10 minutes. A total of 500 µL of isopropanol will be added and inverted 40×, followed by centrifugation at 10,000 rpm and 4 °C for 10 minutes. The samples will be placed in ice without releasing the pellet. The isopropanol will be poured out and the rest will be removed with a 50-µL pipette. Washing will be performed with 200 µL of 70% ethanol carefully so as not do dislodge the pellet. Centrifugation will be performed at 10,000 rpm and 4 °C for 3 minutes. The residual ethanol will be removed and the sample will be left inverted to dry for 30 minutes. Elution will be performed in 40 µL of Tris-EDTA buffer, followed by freezing at −20 °C. The purified DNA will be resuspended in Tris-EDTA buffer. Levels of *Porphyromonas gingivalis, Tannerella forsythia*, and *Treponema denticola* will be determined by quantitative PCR. The quantitative analysis will be performed by real-time PCR using a Step One Plus Real-Time PCR System thermocycler (Applied Biosystem, Foster City, CA) and the products will be detected by fluorescence using the Quantimix Easy SYG Kit (Biotools, Madrid, Spain), following the manufacturer’s protocol. For the reaction, 10 µL of SYBR Green, 0.5 µL of DNA mold and 200 mM of each primer (*P gingivalis* CATAGATATCACGAGGAACTCCGATT and AAACTGTTAGCAACTACCGATGTGG; *T forsythia* GGGTGAGTAACGCGTATGTAACCT and ACCCATCCGCAACCAATAAA; *T denticola* CGTTCCTGGGCCTTGTACA and TAGCGACTTCAGGTACCCTCG; and the universal primers for bacteria CCATGAAGTCGGAATCGCTAG and GCTTGACGGGCGGTGT) will be used in a total volume of 20 µL. Sterile Milli-Q water rather than DNA mold will be used as the negative control. Reactions for 16S rRNA will be performed with initial denaturation at 95 °C for 2 minutes, followed by 36 cycles of 94 °C for 30 seconds, 55 °C for 1 minute and 72 °C for 2 minutes and final extension at 72 °C for 10 minutes. Fluorescence will be detected after each cycle and represented in a graph using the Step One Plus Real-Time PCR System (Applied Biosystem). To ensure the specificity of the products detected by fluorescence and avoid the detection of primer dimers, detection will be performed 1 degree below the dissociation temperature of the amplicons. All samples will be analyzed in duplicate and each dilution of plasmids for the standard curve will be analyzed in triplicate.^[3]^ The purpose of the microbiological analysis will be to determine the effectiveness of photodynamic therapy for the treatment of halitosis, complementing the clinical assessment.

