### 2.9. Statistical analysis

Data from the portable Breath-Alert™ device will be analyzed for normality using the Shapiro–Wilk test. Parametric data will be submitted to analysis of variance followed by Tukey’s test when necessary and the *t* test will be used for paired data to analyze the results of treatment in the 2 periods of the study. Nonparametric data will be compared using the Kruskal–Wallis test followed by the Student–Newman–Keuls test when necessary and the Wilcoxon text will be used for the comparison of each treatment in the 2 periods of the study.

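### The assessment schedule contradicts itself: three times in the Abstract and 2.7, two for microbiological samples in 2.8.3, and an unnamed pair of periods for the within-group tests in 2.9

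*Protocol article*

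**What the plan says.** The protocol article describes the timing of assessments in five places.

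- **Abstract, Methods.** Three times for both types of measurement: "The use of a breath meter and microbiological analysis of the tongue coating will be performed before, immediately after treatment and 7 days after treatment".
- **2.7 Randomization.** Three times for breath, "Breath meter results will be determined before, immediately after treatment and 7 days after treatment", and then for microbiology: "Microbiological analysis of the tongue coating will performed at the same times". The section adds that quantification will use both direct plating and real-time PCR.
- **2.8.3 Microbiological analysis.** Two times: "Microbiological collections will be performed before and immediately after treatment". The rest of the section describes a swab in Amies medium that is plated and cultured anaerobically.
- **2.8.4 Real-time PCR.** A separate swab, placed in Tris-EDTA buffer and frozen. No collection times are given.
- **2.9 Statistical analysis.** The section opens with the breath-meter data. Between-group tests (analysis of variance or Kruskal–Wallis) are tied to no particular time. The within-group tests are tied to two: the Wilcoxon test "will be used for the comparison of each treatment in the 2 periods of the study", and the paired t test is limited in the same way. The two periods are not identified. The Abstract, by contrast, speaks of the different periods and does not limit them to two.

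**The concern.** This is a conflict between positive statements, so it differs from detail that an article may leave to a fuller document. Two parts of the text promise a 7-day microbiological sample, and the operational section omits it. Staff who work from 2.8.3 would not take that sample, and a missed swab cannot be recovered later.

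The day-7 information matters to the trial's own reasoning. The Introduction says "The major challenge is the development of an effective, lasting treatment protocol for halitosis in children" and gives recolonization of the microbiota as part of the case for probiotics. The probiotic course itself lasts 7 days (2.8.7). If assessments are counted from the clinic session, a sample taken straight afterwards could say little about that course.

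The wording in 2.9 raises a second problem. Two-period paired tests do not fit a three-time schedule unless the pair is named. Baseline versus immediately after, baseline versus day 7, and immediately after versus day 7 answer different questions. Left open, the pair can be chosen once the results are known.

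**Working it through.** **Inputs**

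- Children: 4 groups of 13 (2.6), so 4 × 13 = 52, which agrees with the total stated in 2.6, 2.7 and the Abstract.
- Times promised for microbiology: 3 (Abstract, 2.7).
- Times at which 2.8.3 collects samples: 2.
- Times for breath: 3 (Abstract, 2.7).
- Periods in the paired tests: 2, not named (2.9).

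**The statements side by side**

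| Place | Breath | Microbiology | Day 7 included? |
|---|---|---|---|
| Abstract | 3 times | 3 times | yes, both |
| 2.7 | 3 times | 3 times | yes, both |
| 2.8.3 | – | 2 times | no |
| 2.8.4 (PCR) | – | none stated | unclear |
| 2.9, paired tests | 2 periods, not named | – | unclear |
| 2.9, between-group tests | no time stated | – | possible |

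**Microbiology occasions** (children × times; one occasion may involve a culture swab and a PCR swab)

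- Promised: 52 × 3 = 156.
- Under 2.8.3: 52 × 2 = 104.
- Difference: 156 − 104 = 52, and 52 / 156 = one third. All 52 fall at day 7.

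This is an upper figure. The two-time sentence sits in the culture section. If the PCR swabs follow the three times in 2.7, day-7 PCR data would exist and only the culture counts would be missing.

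**Within-group comparisons**

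- Pairs available from three times: 3 × 2 / 2 = 3 per group, so 3 × 4 = 12 over the four groups.
- Pairs provided for by a two-period test: 1 per group, so 4 over the four groups.

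Section 2.9 therefore covers one of three possible pairs per group and leaves open which one. None of this depends on how n = 13 was derived.

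**The case against.** The strongest reply is that the 7-day sample is stated twice and that 2.8.3 does not say the two collections are the only ones. Its sentence may simply be incomplete. The SPIRIT figure (Figure 1) is not shown and may list the assessment times, and the choice of a pair of time points is often left to an analysis plan. It is also fair that the stated objective concerns photodynamic therapy, given in one session, and that 2.8.4 describes the microbiology as serving that question. Samples before and immediately after do inform it.

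Much of this stands, and it limits the point. It does not remove the conflict: two different schedules are written down, and the number of periods in 2.9 does not match the number of times in 2.7. An analysis plan could name the pair, but it could not recover a sample that was never taken.

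Several stronger readings are tempting, and the document does not support them:

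- *That the 7-day result will go untested.* The between-group tests in 2.9 are not confined to any time and can be run at day 7. The unnamed pair may itself be baseline versus day 7.
- *That all later microbiological information will be lost.* The PCR times are not stated in 2.8.4, and 2.7 schedules plating and PCR at all three times.
- *That the post-treatment swab is certainly taken minutes after a clinic session.* The text does not say what immediately after treatment is counted from in the probiotic groups, where the course runs for 7 days.
- *That a family-wise error rate for 12 within-group tests can be charged to the plan.* The plan does not state 12 tests, and the three pairs within a group share the same readings, so a calculation assuming independence would not apply.

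**Conclusion.** The point holds as an unresolved contradiction in the current text about the number and identity of the assessment times. If 2.8.3 is followed as written, up to 52 of 156 child-by-time microbiology occasions are lost, all at day 7. The loss is certain only for culture and depends for PCR on what 2.8.4 intends. If 2.7 is followed, nothing is lost. The sample is therefore at risk, which is less than saying that it will be absent. For breath, all three readings are scheduled without conflict. The defect there is that the within-group tests cover one unidentified pair out of three.

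The counts assume that all 52 children attend every assessment. The change should be made before sampling starts. It does not call the between-group comparison into question.

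**What to change.** 1. **2.8.3:** list all three collection times (before, immediately after and 7 days after treatment), in line with 2.7 and the Abstract.
2. **2.8.4:** state that the PCR swabs are taken at the same three times.
3. **Time origin:** state what the two post-treatment assessments are counted from in each group, since the single photodynamic session (2.8.5), the 7-day probiotic course (2.8.7) and the 10 days of brushing (2.8.8) end at different points. Check that Figure 1 agrees.
4. **2.9:** replace the reference to two periods with named comparisons: baseline versus immediately after, and baseline versus 7 days. Designate one as main in advance and adjust for multiplicity. A repeated-measures analysis over the three times, or a rank-based equivalent such as the Friedman test, would serve as well. The breath score runs only from 0 to 5, so no particular model is required. What matters is that the times are named in advance. Bring the Abstract's wording into line.

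The cost is a few sentences. Section 2.7 already commits to the 7-day assessment, so no new visit is needed. If the laboratory planned for two collections only, the extra work is up to 52 further occasions. If two collections were in fact intended, the Abstract and 2.7 must be changed instead, and the article should then say that no microbiological data will be available at day 7.

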#### 2.8.4. Microbiological analysis—real-time PCR.

The samples of coated tongues will be collected with a sterile swab that will be placed in contact with the surface of the dorsum of the tongue with back-and-forth movements. The samples will be placed in tubes containing Tris–EDTA buffer (10 mM Tris—HCL, 0.1 mM EDTA, pH 7.5). The tubes will be duly labeled and stored at −80 °C until analysis. Maximum storage time will be 1 week. The samples will be frozen due to the impossibility of performing all analyses on a single day. After thawing, the samples will be vortexed for 1 minute. The Master Pure DNA Extraction kit (Epicentre Technologies, Chicago, IL) will be used for the extraction of bacterial DNA. First, 100 μL of sample will be eluted in Tris-EDTA buffer. The samples will be centrifuged at 10,000 rpm and 4 °C for 10 minutes. Next, the MIX will be prepared by diluting 300 µL of TCL + 2 µL of Prot K for each sample. The supernatant will be removed with a pipette, with a volume of 25 µL + the formed pellet remaining. Vortexing will be performed for 10 seconds to resuspend the pellet. A total of 302 µL of MIX will be added to each sample, followed by vortexing for 10 seconds and incubation at 65 °C for 15 minutes with vortexing every 5 minutes. The samples will be placed in ice for 5 minutes. A total of 150 µL of MPC (protein precipitation reagent) will be added to the samples, followed by vortexing for 10 seconds. The samples will be centrifuged at 10,000 rpm and 4 °C for 10 minutes. The supernatant will be removed and placed in a new tube, to which 25 µL of MPC (protein precipitation) will be added. The tube will be centrifuged at 10,000 rpm and 4 °C for 10 minutes. A total of 500 µL of isopropanol will be added and inverted 40×, followed by centrifugation at 10,000 rpm and 4 °C for 10 minutes. The samples will be placed in ice without releasing the pellet. The isopropanol will be poured out and the rest will be removed with a 50-µL pipette. Washing will be performed with 200 µL of 70% ethanol carefully so as not do dislodge the pellet. Centrifugation will be performed at 10,000 rpm and 4 °C for 3 minutes. The residual ethanol will be removed and the sample will be left inverted to dry for 30 minutes. Elution will be performed in 40 µL of Tris-EDTA buffer, followed by freezing at −20 °C. The purified DNA will be resuspended in Tris-EDTA buffer. Levels of *Porphyromonas gingivalis, Tannerella forsythia*, and *Treponema denticola* will be determined by quantitative PCR. The quantitative analysis will be performed by real-time PCR using a Step One Plus Real-Time PCR System thermocycler (Applied Biosystem, Foster City, CA) and the products will be detected by fluorescence using the Quantimix Easy SYG Kit (Biotools, Madrid, Spain), following the manufacturer’s protocol. For the reaction, 10 µL of SYBR Green, 0.5 µL of DNA mold and 200 mM of each primer (*P gingivalis* CATAGATATCACGAGGAACTCCGATT and AAACTGTTAGCAACTACCGATGTGG; *T forsythia* GGGTGAGTAACGCGTATGTAACCT and ACCCATCCGCAACCAATAAA; *T denticola* CGTTCCTGGGCCTTGTACA and TAGCGACTTCAGGTACCCTCG; and the universal primers for bacteria CCATGAAGTCGGAATCGCTAG and GCTTGACGGGCGGTGT) will be used in a total volume of 20 µL. Sterile Milli-Q water rather than DNA mold will be used as the negative control. Reactions for 16S rRNA will be performed with initial denaturation at 95 °C for 2 minutes, followed by 36 cycles of 94 °C for 30 seconds, 55 °C for 1 minute and 72 °C for 2 minutes and final extension at 72 °C for 10 minutes. Fluorescence will be detected after each cycle and represented in a graph using the Step One Plus Real-Time PCR System (Applied Biosystem). To ensure the specificity of the products detected by fluorescence and avoid the detection of primer dimers, detection will be performed 1 degree below the dissociation temperature of the amplicons. All samples will be analyzed in duplicate and each dilution of plasmids for the standard curve will be analyzed in triplicate.^[3]^ The purpose of the microbiological analysis will be to determine the effectiveness of photodynamic therapy for the treatment of halitosis, complementing the clinical assessment.

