Conventional treatments used in the control of halitosis consist basically of the use of toothpastes and mouthwashes containing bactericidal substances, a tongue scraper, the treatment of dental caries and periodontal disease and the control of xerostomia.^[26]^ Some studies suggest that amine fluoride has a positive effect on diminishing halitosis.^[3]^ Alternative treatments, such as antimicrobial photodynamic therapy (aPDT)^[10,21,27]^ and probiotics, have also been employed in an attempt to control this condition.^[3,16,22,23,26]^ Antimicrobial PDT is treatment in which a photosensitizing agent (dye) produces oxygen free radicals in the presence of light, leading to bacterial cell death. As the main etiological factor of halitosis is the presence of anaerobic bacteria, aPDT (red laser and methylene blue) has demonstrated positive results on the reduction of hydrogen sulfide as well as the bacterial load on the dorsum of the tongue.^[15,21]^ The dye annatto has been evaluated as a photosensitizer in studies on halitosis. This extract from the seeds of the plant Bixa orellana, which is native to Brazil, is accepted by the World Health Organization due to the fact that it is nontoxic.^[1]^ Annatto has antioxidant and antimicrobial properties^[9]^ and recent studies have demonstrated its potential as a therapeutic agent and natural dye.^[28]^

Probiotics are microorganisms that provide health benefits when absorbed by the host and are often used in foods and fermented products as well as pharmaceutical formulations.^[25]^ Studies have shown the positive results of probiotics for the control of halitosis and suggest that these products favor the elimination of undesirable microorganisms and promote the recolonization of the microbiota.^[16,22]^

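### Total-DNA qPCR on the swab taken immediately after aPDT may largely miss killing of the three named species, for which it is the only measure

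*Protocol article*

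**What the plan says.** The Introduction describes aPDT as generating oxygen free radicals, "leading to bacterial cell death". Section 2.8.5 has the excess photosensitizer aspirated without water before irradiation, and describes no rinsing or removal of coating afterwards.

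Section 2.8.4 sets out the qPCR workflow in detail. A commercial kit "will be used for the extraction of bacterial DNA", and levels of *P. gingivalis*, *T. forsythia* and *T. denticola* "will be determined by quantitative PCR". No viability dye, RNA target or other live/dead step appears. The section ends: "The purpose of the microbiological analysis will be to determine the effectiveness of photodynamic therapy for the treatment of halitosis", as a complement to the clinical assessment.

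Section 2.8.3 describes the other microbiological measure, a colony count on sheep blood agar under anaerobic incubation. It does not identify species.

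On timing, section 2.7 says "Breath meter results will be determined before, immediately after treatment and 7 days after treatment" and then "Microbiological analysis of the tongue coating will performed at the same times". The Abstract agrees. Section 2.8.3 says "Microbiological collections will be performed before and immediately after treatment" and mentions no 7-day sample.

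On scraping, section 2.7 lists the tongue scraper for Group 1 only, whereas section 2.8.6 has it done on every participant.

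**The concern.** A total-DNA assay counts genome copies whether or not the cell that held them is alive. aPDT is described as killing cells, with little described that would remove them before the immediate swab. Killed cells that stay intact on the tongue are collected, extracted and amplified with the survivors. Scraping acts by taking material away, so its effect appears in full on DNA and on culture alike.

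At the immediate visit the same assay therefore reads the two mechanisms differently. A flat species-level qPCR result could be reported as failure of aPDT against the named organisms when the assay could not tell. If only Group 1 is scraped, a comparison of arms on that reading could also favour scraping for reasons of measurement. If section 2.8.3 governs the sampling times, this reading is the only post-treatment qPCR value in the trial.

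The workflow is stated step by step, so this is a property of the chosen method and not detail that an article leaves to a fuller document.

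**Working it through.** The documents give no kill fraction, DNA recovery or amount of coating removed, so there is no figure of the plan's own to reproduce on this point. The values below are assumptions, chosen to show the range.

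**Inputs (assumed)**
- k, fraction of bacteria killed by aPDT: 0.90 and 0.99.
- f, fraction of dead-cell DNA still recovered and amplified from the immediate swab: 1 down to 0.
- r, fraction of coating removed by scraping: 0.30, 0.50, 0.70.

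**Formulas (log10 fall from baseline)**
- Culture after aPDT: −log10(1 − k).
- qPCR after aPDT: −log10(1 − k + k·f), that is, survivors plus dead cells whose DNA is still recovered.
- Either measure after scraping: −log10(1 − r).

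**aPDT**

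| k | culture | qPCR, f = 1 | f = 0.9 | f = 0.5 | f = 0.1 | f = 0 |
|---|---|---|---|---|---|---|
| 0.90 | 1.00 | 0.00 | 0.04 | 0.26 | 0.72 | 1.00 |
| 0.99 | 2.00 | 0.00 | 0.05 | 0.30 | 0.96 | 2.00 |

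For example, with k = 0.90 and f = 0.9: 1 − 0.90 + 0.81 = 0.91, and −log10(0.91) = 0.04.

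**Scraping**, same value on both measures: r = 0.30 gives 0.15, r = 0.50 gives 0.30, r = 0.70 gives 0.52.

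**When would qPCR place scraping above aPDT?** When 1 − k + k·f > 1 − r, which rearranges to f > (k − r)/k.
- r = 0.50: (0.90 − 0.50)/0.90 = 0.44 and (0.99 − 0.50)/0.99 = 0.49.
- r = 0.30: (0.90 − 0.30)/0.90 = 0.67 and (0.99 − 0.30)/0.99 = 0.70.

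Against scraping that removes half the coating, the order on qPCR reverses once more than about 44% to 49% of dead-cell DNA is recovered, although culture would show 1.00 to 2.00 for aPDT against 0.30. At f = 0.1 it does not reverse even against scraping that removes 70%: with 90% kill, qPCR shows 0.72 against 0.52.

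**The case against.** The strongest reply is that the microbiological analysis is not qPCR alone. The purpose sentence covers the colony count too, and culture on the immediate sample does register killing. That stands. A reader might infer that the trial's microbiology as a whole is blind to aPDT; the documents do not support this. What culture cannot supply is a result for the three named species.

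A reader might also infer that the qPCR cannot register killing at all. That is too strong. Section 2.8.4 discards the supernatant before lysis, which can lose DNA released from ruptured cells, and section 2.8.5 aspirates some material from the tongue. Both lower f by an amount the documents do not state. Neither is a live/dead separation: the supernatant step follows freezing and thawing, and dead cells that remain intact pellet with the live ones.

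A third tempting inference is that scraping will be ranked above aPDT. This needs f above the thresholds and scraping confined to Group 1. If all participants are scraped, as section 2.8.6 says, removal is common to every arm and the ranking argument falls away, while the understatement of killing remains.

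The size is also easily misread. With 90% to 99% killed against 50% removed, survivors differ 5- to 50-fold (0.50/0.10 and 0.50/0.01), but the load eliminated differs only 1.8- to 2.0-fold (0.90/0.50 and 0.99/0.50).

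Finally, the microbiology is described as complementary and section 2.9 names only the breath-meter data. That is correct, and it limits the consequence. An article may also leave the handling of discordant culture and qPCR results to a fuller document, so no fault is found on that score.

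**Conclusion.** The point holds in limited form. On the swab taken immediately after aPDT, the qPCR as described may greatly understate killing of *P. gingivalis*, *T. forsythia* and *T. denticola*, and nothing else in the plan measures those species. With a 90% kill, the qPCR fall could lie anywhere from 0.00 to 1.00 log10 depending on how much dead-cell DNA is recovered, against a fixed 1.00 on culture. The immediate value therefore cannot be read as evidence for or against killing.

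The conclusion rests on aPDT leaving most killed cells in place, which the described procedure suggests but does not quantify. A reversed ranking against scraping is possible, not established. The breath-meter outcome and the sample size are untouched. This is a cheap improvement and not a threat to the trial's main comparison.

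**What to change.** In sections 2.7 and 2.8.4, state that:
- the immediate antibacterial effect is judged by viable culture counts;
- the immediate-after qPCR is reported as total DNA load and is not used as evidence for or against killing by aPDT;
- species-level change is judged by qPCR from baseline to 7 days.

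Reconcile section 2.8.3 with the Abstract and section 2.7 on whether a 7-day microbiological sample is taken, and section 2.7 with section 2.8.6 on who is scraped.

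The cost is wording if the 7-day sample is already intended, and an added collection if section 2.8.3 reflects the actual plan. There are two losses. No species-specific result for immediate killing will be available, and the 7-day value also reflects recolonisation, home hygiene and the probiotic course, so it answers a different question. A viability step before DNA extraction would recover the immediate species-level reading, but it is an extra laboratory procedure and is not needed to settle this point.
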